## **4. Patient selection**

### **4.1 Inclusion criteria**

1. Subjects who have fully understood the study and have signed the informed consent form (ICF).
2. Male or female, age over 18 years (including 18) old and no more than 75 years old.
3. Extranodal NK/T-cell lymphoma confirmed by histopathology examination.
4. Refractory and relapsed ENKTCL that has failed the treatment of asparaginase-based chemotherapy or radiochemotherapy.

Definition of refractory:

- i. Failure to get PR after chemotherapy with asparaginase-containing regimen;  
or

- ii. Disease progression within 6 months of the final asparaginase-containing regimen.
5. Subjects with Eastern Cooperative Oncology Group (ECOG) performance status score of 0 or 1;
  6. The expected survival time is over 3 months.
  7. There must be at least 1 evaluable or measurable lesion that meets the RECIL 2017 lymphoma criteria [evaluable lesion: 18F-Fluorodeoxyglucose/Positron Emission Tomography (18F-Fluorodeoxyglucose/Positron Emission Tomography, 18FDG/PET) examination showing increased lymph nodes or extranodal uptake (higher than liver) and PET and/or Computed Tomography (CT) features are consistent with lymphoma manifestations; measurable lesions: nodular lesions longer than 15mm or extranodal lesions longer than 10mm (if the only measurable lesion has received radiotherapy in the past, there must be evidence of radiological progression after radiotherapy) and accompanied by increased 18FDG uptake]. Except for this, there is no measurable increase in the diffuse 18FDG uptake in the liver.
  8. Subjects should have adequate hematological, hepatic, and renal function as defined by the following laboratory examinations. Subjects have not received cell growth factors, platelet or granulocyte infusion within 7 days before hematological examinations (for the long-acting granulocyte-colony stimulating factor [G-CSF] and [PEG-CSF], the interval of 2 weeks is required):
    - a) Absolute neutrophil count  $\geq 1.5 \times 10^9$  / L for subjects without marrow involvement of lymphoma; absolute neutrophil count  $\geq 1.0 \times 10^9$  / L for subjects with marrow involvement;
    - b) Hemoglobin  $\geq 90$  g/ L (without red blood cell infusion within 14 days),

- hemoglobin  $\geq 75$  g/L for subjects without marrow involvement of lymphoma;
- c) Platelet count  $\geq 75 \times 10^9$  / L for subjects without marrow involvement of lymphoma; platelet count  $\geq 50 \times 10^9$  / L for subjects with marrow involvement;
  - d) Upper Limit Normal (ULN), or creatinine clearance ( $\geq 40$  mL/min) of serum creatinine ( $\leq 1.5$  times normal value upper limit) (estimated by the Cockcroft-Gault formula);
  - e) Serum total bilirubin  $\leq 1.5$  times ULN;
  - f) Aspartate Aminotransferase (AST), Alanine Aminotransferase (ALT)  $\leq 2.5$  times ULN;
  - g) Coagulation function: International Normalized Ratio (INR)  $\leq 1.5$  times ULN; Prothrombin Time (PT), Activated Partial Thromboplastin Time (APTT)  $\leq 1.5$  times ULN (unless the subject is receiving anticoagulant therapy and PT and APTT are using anticoagulant therapy at the screening time).
  - h) Thyroid-stimulating hormone (TSH) or free thyroxine (FT4) or free triiodothyronine (FT3) are all within the normal range ( $\pm 10\%$ ).
9. There was no evidence that subjects had difficulty breathing at rest, and the measured value of pulse oximetry at rest was more than 92%;
10. Subjects must pass a pulmonary function test (PFT) to confirm that forced expiratory volume (FEV1)/forced vital capacity (FVC) in the first second is more than 60%, unless it is a large mediastinal mass caused by lymphoma that cannot meet this standard; carbon monoxide diffusion (DLCO), FEV1 and FVC are all above 50% of the predicted value; all PFT results must be obtained within four weeks before the first administration;

11. Subjects who have received anti-tumor therapy should be screened only after the toxicity of the previous treatment has recovered to the grade 1 level or baseline level according to Common Terminology Criteria for Adverse Events (CTCAE) V5.0;
12. Women of Childbearing Potential (WOBCP) must undergo a serum pregnancy test within seven days before the first medication and the results are negative. WOBCP or men and their WOBCP partners should agree to take effective contraceptive measures from the signing of ICF until six months after the last dose of the research drug is used.

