| 4.1 Inclusion criteria
2. Male or female, age over 18 years (including 18) old                                                                                                                                                                                                                                             | 2. Male or female, age over 18 years (including 18) old and no more than 75 years old.                                                                                                                                                                                                                                                                                                                                                                                                                                                                                                                                                     | Extremely low incidence rate in patients over 80 years, and lack of efficacy and safety data in this population. |
| 4.1 Inclusion criteria
9. a) Absolute neutrophil count $\geq 1.5 \times 10^9$ /L for subjects without marrow involvement of lymphoma;
b) Hemoglobin $\geq 90$ g/ L (without red blood cell infusion within 14 days);
c) Platelet count $\geq 75 \times 10^9$ /L for subjects without marrow involvement of lymphoma; | 4.1 Inclusion criteria
9. a) Absolute neutrophil count $\geq 1.5 \times 10^9$ /L for subjects without marrow involvement of lymphoma; absolute neutrophil count <math>\geq 1.0 \times 10^9</math> /L for subjects with marrow involvement;
b) Hemoglobin $\geq 90$ g/ L (without red blood cell infusion within 14 days), hemoglobin <math>\geq 75</math> g/ L for subjects without marrow involvement of lymphoma;
c) Platelet count $\geq 75 \times 10^9$ /L for subjects without marrow involvement of lymphoma; platelet count <math>\geq 50 \times 10^9</math> /L for subjects with marrow involvement; | Give a detailed description of hematological function for patients with marrow involvement.                      |

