|  | 
 
i. Absolute neutrophil count <math>\geq 1.5 \times 10^9 / L</math> for subjects without marrow involvement of lymphoma; absolute neutrophil count <math>\geq 1.0 \times 10^9 / L</math> for subjects with marrow involvement;
 
ii. Hemoglobin <math>\geq 90 \text{ g/L}</math> (without red blood cell infusion within 14 days), hemoglobin <math>\geq 75 \text{ g/L}</math> for subjects without marrow involvement of lymphoma;
 
iii. Platelet count <math>\geq 75 \times 10^9 / L</math> for subjects without marrow involvement of lymphoma; platelet count <math>\geq 50 \times 10^9 / L</math> for subjects with marrow involvement;
 
iv. Upper Limit Normal (ULN), or creatinine clearance (<math>\geq 40 \text{ mL/min}</math>) of serum creatinine (<math>\leq 1.5</math> times normal value upper limit) (estimated by the Cockcroft-Gault formula);
 
v. Serum total bilirubin <math>\leq 1.5</math> times ULN;
 
vi. Aspartate Aminotransferase (AST), Alanine Aminotransferase (ALT) <math>\leq 2.5</math> times ULN;
 
vii. Coagulation function: International Normalized Ratio (INR) <math>\leq 1.5</math> times ULN; Prothrombin Time (PT), Activated Partial Thromboplastin Time (APTT) <math>\leq 1.5</math> times ULN (unless the
 
 |

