16. Patients with active hepatitis B or active hepatitis C. Patients who are positive for hepatitis B Surface Antigen (HBsAg) or hepatitis C Virus (HCV) antibodies

at screening stage must pass further detection of hepatitis B Virus (HBV) DNA titer (no more than 1000 copies/mL or 500 IU/mL) and HCV RNA (no more than the lower limit of the detection method) in the row. In addition to active hepatitis B or hepatitis C infections requiring treatment, group trials can be conducted. Hepatitis B carriers, stable hepatitis B (DNA titer should not be higher than 2500 copies/mL or 500 IU/mL) after drug treatment, and cured hepatitis C patients can be enrolled in the group;

17. Patients with active pulmonary tuberculosis;
18. Known history of hypersensitivity to a similar drug and any excipient in the study drug;
19. Pregnant or lactating women;
20. Have uncontrollable complications, including but not limited to symptomatic congestive heart failure, uncontrollable hypertension, unstable angina, active peptic ulcer or hemorrhagic diseases;
21. Any severe or uncontrolled systematic disease, systematic complication, other severe complicated diseases, or any special condition that might make the subjects unsuitable for the study, or might affect the compliance to the protocol or might cause significant interference in safety/ efficacy evaluation of the study drug as judged by the investigator.

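### The hemoglobin entry limit gives two thresholds to patients without marrow involvement and no relaxed one to patients with it; secondarily, the two HBV DNA caps do not agree

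*Protocol*

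**What the plan says.** **Hemoglobin.** Section 4.1, item 8 b), opens with a limit of 90 g/L. It names no marrow group and carries the condition "without red blood cell infusion within 14 days". The same line continues with "hemoglobin $\geq 75$ g/L for subjects without marrow involvement of lymphoma". The synopsis has the same two limits with the same group attached.

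The neighbouring lines split by marrow status. Line a) requires neutrophils of 1.5 × 10⁹/L without involvement, and then "absolute neutrophil count $\geq 1.0 \times 10^9$ / L for subjects with marrow involvement". Line c) requires platelets of 75 × 10⁹/L without involvement, and then "platelet count $\geq 50 \times 10^9$ / L for subjects with marrow involvement".

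The second limits in a), b) and c) came in with Amendment 01, whose stated reason was: "Give a detailed description of hematological function for patients with marrow involvement".

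**Hepatitis B.** Section 4.2, exclusion 16, first requires patients who test positive for HBsAg at screening to have a "DNA titer (no more than 1000 copies/mL or 500 IU/mL" result. Later in the same item, stable hepatitis B after drug treatment may be enrolled on the condition "DNA titer should not be higher than 2500 copies/mL or 500 IU/mL". The synopsis repeats both.

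**The concern.** These are entry rules, applied patient by patient at several sites. A rule that gives two answers for the same patient leaves the choice to whoever screens, and afterwards to whoever decides whether the enrolment was a protocol deviation.

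The hemoglobin line is the more serious of the two. It conflicts with itself for one marrow group, and for the other it does not deliver what the amendment says it was for. The hepatitis B item has a narrower fault: one IU value is paired with two copy numbers, and the two sentences overlap in one subgroup.

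**Working it through.** No planned statistical figure depends on these lines, so the check compares the text and works out two ratios.

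**Step 1: the three hematology lines side by side (section 4.1, item 8).**

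| Line | Without marrow involvement | With marrow involvement | No group named |
|---|---|---|---|
| a) neutrophils, ×10⁹/L | 1.5 | 1.0 | – |
| b) hemoglobin, g/L | 75 | – | 90 |
| c) platelets, ×10⁹/L | 75 | 50 | – |

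Lines a) and c) give each group one limit, the lower one for patients with involvement. Line b) has no limit specific to that group.

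**Step 2: apply line b) to a patient at 80 g/L, inside the disputed band.**

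| Reading of line b) | Without involvement | With involvement |
|---|---|---|
| 90 applies to everyone; 75 is an additional limit | ineligible (75 has no effect) | ineligible |
| 75 replaces 90 for the group it names; 90 applies to the rest | eligible | ineligible |

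The first reading makes the second half of the line redundant. The second gives patients with involvement the stricter limit, opposite to a) and c). Under either reading a patient with involvement at 80 g/L is excluded, although that is the group named in the amendment rationale. A patient without involvement at 80 g/L changes status with the reading. The disputed band is 75 g/L up to, but not including, 90 g/L (75 to 89 in whole units).

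**Step 3: the HBV DNA pairings (section 4.2, exclusion 16).**

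- HBsAg-positive at screening: 1000 copies/mL ÷ 500 IU/mL = 2 copies per IU.
- Stable after drug treatment: 2500 copies/mL ÷ 500 IU/mL = 5 copies per IU.
- Ratio of the caps in copies/mL: 2500 ÷ 1000 = 2.5.

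No single conversion satisfies both. At 2 copies per IU, 2500 copies/mL is 2500 ÷ 2 = 1250 IU/mL, not 500. At 5 copies per IU, 1000 copies/mL is 1000 ÷ 5 = 200 IU/mL, not 500.

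**Step 4: who is caught.** An HBsAg-positive patient, stable after drug treatment, at 1001 to 2500 copies/mL fails the first sentence and passes the later one. Nothing in the item exempts treated patients from the first sentence.

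**The case against.** **The hemoglobin line can be read without a logical contradiction.** Taking 75 g/L as the limit for the group it names and 90 g/L for everyone else does remove the conflict. It does so only by running against lines a) and c) and against the amendment's stated purpose, and the line does not say that this is the reading. The wording stands in the current section 4.1 and synopsis, so this is not a leftover in the amendment log.

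**The two HBV caps are worded for different situations.** This is largely fair. The 2500 cap is attached to stable hepatitis B after drug treatment. Carriers are mentioned beside it, but no cap is stated for them in that clause. A laboratory reporting in IU/mL sees 500 in both sentences. What stands is the overlap for HBsAg-positive patients who are stable on treatment, and the inconsistent copies-per-IU pairing.

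**Stronger inferences that the documents do not support:**

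- *Patients with marrow involvement are shut out.* They remain eligible at 90 g/L or above; only those from 75 up to 90 g/L are excluded.
- *Every HBsAg-positive patient at 1001 to 2500 copies/mL has two answers.* Only those who are also stable after drug treatment clearly do.
- *Hepatitis B safety screening differs by site.* The tests are common to all sites, and note 15 to the schedule of assessments has HBV-DNA-positive patients monitored every cycle and given nucleoside analogues. Only the enrolment threshold could differ.
- *The efficacy decision is at stake, because section 10.1 requires more than 19 responders among 28.* Any such boundary turns on one responder. Nothing in the protocol links either band to response.

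**Conclusion.** Item 8 b) is wrong as written. It gives patients without marrow involvement two hemoglobin limits and patients with involvement no relaxed one. The affected band is 75 up to 90 g/L: status depends on the reader without involvement, and is exclusion with involvement despite the amendment's stated purpose. The hepatitis B inconsistency is real but secondary, confined to HBsAg-positive, treated-stable patients at 1001 to 2500 copies/mL and to the 2-versus-5 copies-per-IU pairing.

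Sample size, alpha and power are not affected. The protocol gives no distribution of hemoglobin or HBV DNA among candidates, so the number of patients concerned cannot be derived from it. Sites could enrol differently; that they will is not shown. The finding rests only on the wording of the current text. It does not say which limit is right for either group, because the documents do not settle that.

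**What to change.** - **Section 4.1, item 8 b):** reconcile the line so that each marrow group has exactly one hemoglobin limit, and check the result against the purpose stated in Amendment 01.
- **Section 4.2, exclusion 16:** reconcile the two HBV DNA caps. Either state one cap in one unit, or say explicitly which group each cap applies to, with one consistent copies-per-IU pairing.
- **Synopsis:** make the same corrections there.

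The medical lead decides all values and which group each belongs to. The cost is an edit to two items and their copies in the synopsis, submitted through the amendment route in section 11.5. No statistical section changes.

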#### **4.2 Exclusion Criteria:**

1. Invasive natural killer cell leukemia;
2. Active hemophagocytic syndrome (Suffered from hemophagocytic syndrome previously but recovered more than 6 months could enrolled.);
3. Primary central nervous system lymphoma or secondary central nervous system involvement;
4. Received organ transplantation in the past;
5. Patients who received allogeneic hematopoietic stem cell transplantation within three years;
6. Adverse reactions from the previous anti-tumor treatment have not yet recovered to  $\leq$ Grade 1 based on NCI-CTCAE [Version 5.0], except for hair loss and pigmentation;
7. Autologous hematopoietic stem cell transplantation was performed within 90 days before the start of the study;
8. Patients with active autoimmune diseases requiring systematic treatment in the past two years (hormone replacement therapy is not considered systematic

treatment, such as type I diabetes mellitus, hypothyroidism requiring only thyroxine replacement therapy, adrenocortical dysfunction or pituitary dysfunction requiring only physiological doses of glucocorticoid replacement therapy); Patients with autoimmune diseases who do not require systematic treatment within two years can be enrolled;

9. Subjects requiring systemic glucocorticoid therapy or other immunosuppressive therapy for a given condition within 14 days before treatment [allowing subjects to use local, ocular, intra-articular, intranasal and inhaled glucocorticoid therapy (with very low systemic absorption); and allowing short-term (< 7 days) glucocorticoid prophylaxis (e.g., contrast agent overdose) Sensitivity] or for the treatment of non-autoimmune diseases (e.g. delayed hypersensitivity caused by contact allergens);
10. In the past five years, patients with other malignant tumors have undergone radical treatment, except for basal cell carcinoma of skin, squamous cell carcinoma of skin, carcinoma in situ of breast and carcinoma in situ of cervix.
11. Subjects have major surgery within four weeks prior to enrollment or those who have not completely recovered from any previous invasive operation;
12. Uncontrolled hypertension (the systolic pressure > 180 mmHg and/or diastolic pressure >100 mmHg after treatment);
13. Active hemorrhagic diseases;
14. Begin research on live vaccination (except influenza attenuated vaccine) within 28 days before treatment;
15. Human immunodeficiency virus (HIV) infection (HIV positive);
16. Patients with active hepatitis B or active hepatitis C. Patients who are positive for hepatitis B Surface Antigen (HBsAg) or hepatitis C Virus (HCV) antibodies

at screening stage must pass further detection of hepatitis B Virus (HBV) DNA titer (no more than 1000 copies/mL or 500 IU/mL) and HCV RNA (no more than the lower limit of the detection method) in the row. In addition to active hepatitis B or hepatitis C infections requiring treatment, group trials can be conducted. Hepatitis B carriers, stable hepatitis B (DNA titer should not be higher than 2500 copies/mL or 500 IU/mL) after drug treatment, and cured hepatitis C patients can be enrolled in the group;

17. Patients with active pulmonary tuberculosis;
18. Known history of hypersensitivity to a similar drug and any excipient in the study drug;
19. Pregnant or lactating women;
20. Have uncontrollable complications, including but not limited to symptomatic congestive heart failure, uncontrollable hypertension, unstable angina, active peptic ulcer or hemorrhagic diseases;
21. Any severe or uncontrolled systematic disease, systematic complication, other severe complicated diseases, or any special condition that might make the subjects unsuitable for the study, or might affect the compliance to the protocol or might cause significant interference in safety/ efficacy evaluation of the study drug as judged by the investigator.

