**Summary of Changes Table:**

| Section # and Name
(Before modification)                                                                                                                                          | Description of Change                                                                                                                                                  | Brief Rationale                                                                                                     |
|----------------------------------------------------------------------------------------------------------------------------------------------------------------------------------------------|-------------------------------------------------------------------------------------------------------------------------------------------------------------------------------|----------------------------------------------------------------------------------------------------------------------------|
| 4.1 Inclusion criteria
4. Available tumor tissue samples (10-15 unstained, fresh-frozen, paraffin-embedded [FFPE] slides) obtained from past or fresh coarse-needle puncture or excision. | 4. <del>Available tumor tissue samples (10-15 unstained, fresh-frozen, paraffin-embedded [FFPE] slides) obtained from past or fresh coarse-needle puncture or excision.</del> | Tissue specimens not available for some patients                                                                           |
| 4.2 Exclusion Criteria:
4. Received prior therapy with anti-PD-1/L1 antibodies or chidamide;                                                                                              | 4. <del>Received prior therapy with anti-PD-1/L1 antibodies or chidamide;</del>                                                                                               | Due to slow enrollment progress, patients who were previously treated with PD-1/L1 antibodies or chidamide were permitted. |

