**Table 1. Sintilimab Dose Adjustment Principle**

| Adverse events related to sintilimab | Severity                                                                                                                                                                                                                                                          | Dose adjustment           |
|--------------------------------------|-------------------------------------------------------------------------------------------------------------------------------------------------------------------------------------------------------------------------------------------------------------------|---------------------------|
| Pneumonia                            | Grade 2 pneumonia                                                                                                                                                                                                                                                 | suspension a   |
|                                      | Recurrent Grade 2 pneumonia, Grade 3 or 4 pneumonia                                                                                                                                                                                                               | permanent discontinuation |
| Diarrhea or enterocolitis            | Grade 2 or 3 diarrhea or enterocolitis                                                                                                                                                                                                                            | suspension a   |
|                                      | Grade 4 diarrhea or enterocolitis                                                                                                                                                                                                                                 | permanent discontinuation |
| Dermatitis                           | Grade 3 dermatitis                                                                                                                                                                                                                                                | suspension a   |

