|                                      | Grade 4 dermatitis                                                                                                                                                                                                                                                | permanent discontinuation |
| Hepatitis                            | For subjects with normal baseline ALT, AST, or TBIL, Grade 2 elevation of AST, ALT, or TBIL. For subjects with baseline AST, ALT, or TBIL>ULN, $\geq 50\%$ increase of AST, ALT or TBIL (to meet the requirements of Grade 2) and duration less than 7 days.      | suspension a   |
|                                      | For subjects with normal baseline ALT, AST, or TBIL, Grade 3 or 4 elevation of AST, ALT, or TBIL. For subjects with baseline AST, ALT, or TBIL>ULN, $\geq 50\%$ increase of AST, ALT or TBIL (to meet the requirements of Grade 3 or 4) and duration over 7 days. | permanent discontinuation |
| Hypophysitis                         | Grade 2 hypophysitis                                                                                                                                                                                                                                              | suspension b   |

|                       |                                                                                                                                |                                        |
|-----------------------|--------------------------------------------------------------------------------------------------------------------------------|----------------------------------------|
|                       | Grade 3 or 4 hypophysitis                                                                                                      | permanent discontinuation              |
| Adrenal insufficiency | Grade 2 adrenal insufficiency                                                                                                  | suspension b                |
|                       | Grade 3 or 4 adrenal insufficiency                                                                                             | permanent discontinuation              |
| Hyperthyroidism       | Grade 3 or 4 hyperthyroidism                                                                                                   | permanent discontinuation              |

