| Type 1 diabetes       | Grade 3 hyperglycemia                                                                                                          | suspension b                |
|                       | Grade 4 hyperglycemia                                                                                                          | permanent discontinuation              |
| Renal insufficiency   | Grade 2 or 3 Elevated creatinine                                                                                               | suspension a                |
|                       | Grade 4 Elevated creatinine                                                                                                    | permanent discontinuation              |
| Neurotoxicity         | Grade 2 neurotoxicity                                                                                                          | suspension a                |
|                       | Grade 3 or 4 neurotoxicity                                                                                                     | permanent discontinuation              |
| Other AEs             | First appearance of other Grade 3 AEs                                                                                          | suspension a                |
|                       | Recurrence of the same Grade 3 AE                                                                                              | permanent discontinuation              |
|                       | Grade 3 AE: Failure to decrease to Grade 0-2/baseline level within 7 days or return to Grade 0-1/baseline level within 14 days | permanent discontinuation              |
|                       | Grade 4 AE                                                                                                                     | permanent discontinuation c |

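### Since Amendment 02, a patient who has recovered from a serious toxicity on an earlier PD-1/L1 antibody is not clearly excluded, although the same kind of event on study would end sintilimab for good

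*Protocol*

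**What the plan says.** The summary of changes for Amendment 02 strikes out the former exclusion of earlier anti-PD-1/L1 or chidamide treatment. The reason given is slow enrollment: "patients who were previously treated with PD-1/L1 antibodies or chidamide were permitted". The current section 4.2 has no such item and nothing in its place.

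Two criteria deal with toxicity left over from earlier treatment:

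- 4.2 item 6 excludes patients in whom "Adverse reactions from the previous anti-tumor treatment have not yet recovered to" grade 1 or less, with hair loss and pigmentation excepted.
- 4.1 item 11 says that pretreated patients "should be screened only after the toxicity of the previous treatment has recovered to the grade 1 level or baseline level".

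For events on study, Table 1 in section 5.5, whose first column is headed "Adverse events related to sintilimab", lists what suspends sintilimab and what ends it. Permanent discontinuation applies, for example, to "Recurrent Grade 2 pneumonia, Grade 3 or 4 pneumonia", "Grade 3 or 4 neurotoxicity" and "Grade 4 Elevated creatinine". Section 5.13 adds a short list of grade 3-4 events related to the study drug that also end dosing permanently.

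**The concern.** Before Amendment 02 nobody with earlier exposure to the class could enter, so past class toxicity did not need its own criterion. The amendment made it relevant, but the eligibility text still looks only at how far the patient has recovered. On study, the protocol treats certain events as serious enough that later recovery does not reopen dosing. At entry, recovery satisfies both toxicity criteria, even if the event came from another antibody of the same class.

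Patient safety and uniform practice across centers are at stake. Two investigators could apply section 4 to the same patient and reach opposite decisions, each with support in the text.

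**Working it through.** No arithmetic applies beyond a count. The check reads every criterion in 4.1 and 4.2 against the permanent-discontinuation events in Table 1 and 5.13.

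**Step 1: the working limit on past toxicity.** Both 4.1 item 11 and 4.2 item 6 must be met. A patient back at a baseline of grade 2 passes item 11 but fails item 6. The limit in practice is therefore grade 1 or less. Both items test the present grade. Neither mentions the worst past grade, the type of event, or whether the earlier drug was stopped because of it.

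**Step 2: events that end sintilimab for good on study.**

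- Table 1, non-endocrine rows: pneumonia (recurrent grade 2, or grade 3-4), diarrhea/enterocolitis (grade 4), dermatitis (grade 4), hepatitis (grade 3-4), renal insufficiency (grade 4 creatinine) and neurotoxicity (grade 3-4). That is 6.
- Named only in 5.13: grade 3-4 decrease of cardiac function and grade 3-4 pancreatitis. That is 2, so 6 + 2 = 8.
- Table 1, endocrine rows: hypophysitis, adrenal insufficiency and hyperthyroidism (each grade 3-4) and grade 4 hyperglycemia. That is 4, so 8 + 4 = 12 named types.
- Not counted: the general rows for other events in Table 1, and allergic reactions in 5.13, which overlap with 4.2 item 18 (hypersensitivity to a similar drug).

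**Step 3: does recovery reopen dosing on study?** No. Notes a and b, which allow sintilimab to be resumed, are attached to suspension rows only. Note c gives some discretion over grade 4 laboratory findings, but it is attached only to the grade 4 row for other events.

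**Step 4: apply section 4 to two patients.** Patient A had grade 3 hepatitis on an earlier PD-1 antibody. It was treated with steroids within the past two years, the course ended more than 14 days before study treatment, and liver values are now normal. Patient B had the same event, but it settled without systemic treatment.

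| Criterion | Patient A | Patient B |
|---|---|---|
| 4.1 item 11, 4.2 item 6 (present grade) | passes | passes |
| 4.1 items 8 to 10 (current laboratory, oximetry, lung function) | not barred by the past event | not barred by the past event |
| 4.2 item 9 (steroids within 14 days) | passes | passes |
| 4.2 item 18 (hypersensitivity) | does not apply | does not apply |
| 4.2 item 8 (autoimmune disease, two-year look-back) | unclear | not reached |
| 4.2 item 21 (investigator's judgment) | may refuse, need not | may refuse, need not |

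Item 8 is unclear for patient A because it speaks of active autoimmune disease and does not name immune-related adverse events, while its two-year window turns on treatment history.

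**Step 5: what screening records.** Section 6.1 item 3 asks for the dates of earlier treatment, the best response and the date of progression, but not the reason for stopping. Item 2 may capture the event as medical history, but it does not require a link to the antibody.

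**The case against.** The strongest reply rests on exclusion 8. It looks back two years for systemic treatment, and its closing sentence makes the need for such treatment the dividing line for enrollment. Section 5.5 shows that the protocol expects immune-related events to be treated with glucocorticoids. An investigator could therefore reasonably exclude a patient with recently treated, resolved pneumonitis or hepatitis. This stands in part. A reader might infer that only exclusion 21 keeps such a patient out, and the text does not support a statement that absolute. But the word active, and the absence of any mention of immune-related events, leave the coverage arguable. Events without recent systemic treatment are not reached.

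A second reply is that Table 1 and 5.13 concern sintilimab and the study drug, and nothing in the protocol says that a resolved event on another antibody predicts recurrence. That is correct. A reader might infer that section 4 contradicts those stopping rules. It does not, because they govern events on study and are silent on entry. Carrying them over to past treatment is a clinical judgment about the class.

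Two further readings go too far:

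- A reader might take exclusion 6 to accept a return to baseline. Only inclusion 11 has that alternative.
- A reader might want every permanent-discontinuation row of Table 1 to become an exclusion. The general rows depend on recurrence and on recovery within 7 or 14 days, which may not be recoverable from treatment given elsewhere. The endocrine rows, such as "Grade 3 or 4 adrenal insufficiency", would bar patients whose hormone-replaced condition exclusion 8 deliberately tolerates.

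**Conclusion.** The point holds as a safety gap in eligibility and should be corrected. Followed as written, section 4 can lead to sintilimab being given after a recovered class-related event of a kind that would have ended it permanently on study. No criterion clearly prevents this.

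The gap covers eight named non-endocrine event types. That is a count of protocol categories and measures neither patients nor risk. The number of patients concerned is not given and cannot be derived. The conclusion assumes that serious toxicity on one PD-1/L1 antibody bears on the safety of another. This is a clinical premise that the protocol neither states nor denies. If the sponsor considers rechallenge acceptable for some of these events, the protocol should say so and set conditions.

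A reader might infer that the phase II result is affected. It is not: the sample size, the stopping rule, the error rates and the estimate of the response rate do not depend on this point.

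**What to change.** Add one item to 4.2. Exclude patients who, related to an earlier PD-1/L1 antibody, had any of the following, or whose earlier antibody was permanently stopped for such an event:

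- grade 3-4 pneumonia, hepatitis, pancreatitis, neurotoxicity or decrease of cardiac function;
- recurrent grade 2 pneumonia;
- grade 4 diarrhea/enterocolitis, dermatitis or creatinine elevation.

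State an exemption for endocrine events controlled on physiological hormone replacement, and base it on exclusion 8. Note b of Table 1 cannot carry it, because that note is attached only to suspension rows. Do not import the time-based rows for other events.

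Optionally, have 6.1 item 3 record why each earlier PD-1/L1 antibody was stopped, so that the new item can be applied from the record.

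The cost is one exclusion item and, if wanted, one case report form field. Some pre-exposed patients, number unknown, would become ineligible in a trial that was opened to them because enrollment was slow.
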